### Data Security

After completing fundus photography, image files are automatically sent to the PACS for both the intervention and control groups or the AI PACS for only the intervention group. To protect patient privacy, secure the medical device and software, and maintain hospital information system stability, this study will apply to the Center of Intelligent Healthcare at NTUH for the “Trial Use of AI/Machine Learning Medical Device Software.” This step will verify that VeriSee DR and VeriSee AMD meet all relevant regulations, allowing their safe and effective use in clinical practice.

Study-related data will be managed using REDCap, a secure, web-based electronic data management system. REDCap will be used to record participant eligibility assessment, randomization assignments, physician interpretation results, and AI-generated screening outputs. Research data collected in REDCap will be stored separately from the hospital clinical information systems, with access restricted to authorized study personnel through role-based permissions. All data handling procedures will comply with institutional data protection policies and relevant data privacy regulations.

### Statistical Analysis

Baseline characteristics of the 2 study groups will be summarized as percentages for categorical variables and as means with SDs for continuous variables. Categorical variables will be compared using the chi-square test, and continuous variables will be compared using the 2-tailed *t* test. The primary analysis will follow the intention-to-screen principle, in which all randomized participants are analyzed according to their assigned study arm regardless of adherence to subsequent screening and management processes. Thus, participants will remain in the primary analysis regardless of whether AI interpretation is successfully completed, whether referral is achieved after a positive test result, or whether missing data occur within the screening workflow. These participants will still be included in the analysis of the primary outcome estimates, namely the detection rates. A per-protocol analysis will also be conducted, including only participants who adhered to the predefined study procedures, namely successful AI interpretation and, for those with positive test results, successful referral for further evaluation. Participants with any missing data during the process will be excluded from the per-protocol analysis. This population will be used to assess secondary outcome estimates, namely the PPVs. Between-group comparisons of primary and secondary outcomes will be performed using the 2 sample proportional tests.

Although the study adopted a multicenter pragmatic design, randomization was conducted at the individual level. The AI instruments are assumed to perform consistently across different settings. Therefore, the primary analyses of the primary outcomes will be conducted as crude analyses without adjustment for potential differences in baseline characteristics or workflow processes between the study groups. Nonetheless, hospital site effects, physician-level variation, image quality, referral completion, and missing confirmatory diagnoses may have been imbalanced between groups during study execution in this pragmatic setting and could potentially confound the primary analyses. Therefore, subsidiary analyses will be conducted at both the participant and physician levels using predefined subgroup analyses to examine the consistency of screening effects across primary outcomes. These subgroups will include study site, image quality (participants with and without poor-quality images for which AI could not generate a report despite repeat testing), referral timeliness (with delayed referral defined as no referral within 2 mo), physician specialty (including family medicine and geriatric or gerontology care physicians), clinical setting (across the 4 participating hospitals), and participant-level characteristics (including age, sex, and comorbidities). These subsidiary analyses are exploratory in nature, and results will be presented descriptively without adjustment for multiple comparisons.

In addition to the originally planned 2-sample proportion comparisons in the randomized trial and subsidiary stratified analyses, post hoc multivariable regression models will be performed to account for potential clustering and confounding factors and to support the findings from the primary analyses. Site-level variability and physician-level effects will be addressed using mixed-effects models, with study site and/or physician included as random effects where appropriate. Adjustment for relevant covariates, including baseline characteristics of patients, image quality, referral completion status, and missing confirmatory diagnoses, will also be performed. Effect estimates will be reported as adjusted odds ratios with corresponding 95% CIs.

In addition, regarding the incomplete referral follow-up and missing confirmatory diagnoses in the pragmatic setting, the number and proportion of participants with missing outcome data will be summarized by study group, together with the reasons for missingness whenever available. The primary detection rate analysis will follow the intention-to-screen principle, in which screen-positive participants with missing confirmatory diagnosis will remain in the denominator but will not contribute to the numerator. For PPV analyses, participants with missing confirmatory diagnosis will be excluded from both the numerator and denominator. Post hoc mixed-effects regression analyses will be performed for these 2 outcomes accounting for other covariates as mentioned earlier.

A 2-sided *P* value of <.05 will be considered statistically significant. All statistical analyses will be conducted using the SAS software (version 9.4; SAS Institute).

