**Figure 4. F4:**

Workflow of artificial intelligence (AI)–assisted fundus screening integrated with Picture Archiving and Communication System (PACS) and electronic health record (EHR).

The clinical workflow begins with the physician issuing an AI-assisted fundus photography order, followed by fundus photography acquisition and image upload to the PACS. The AI system then retrieves the images and triggers randomization via the AIMIGS system. In the experimental group, images undergo AI analysis, and the results are uploaded back to AI PACS. In the control arm, images are not analyzed by AI. Finally, physicians review the results in the EHR.

When a fundus image is considered insufficient for clinical interpretation, trained health care personnel will immediately reacquire the image on-site and reassess its quality. This process will not require any additional clinic visits or rescheduling. In both the AI-assisted and conventional screening arms, retinal imaging, image interpretation, and referral decisions are performed identically, ensuring that both groups follow the same care pathway at the same clinical time point. Both study arms follow an identical workflow. The only difference between groups is that the AI-assisted arm provides an additional AI-generated output to support physician decision-making, whereas the control arm relies solely on physician interpretation without AI assistance.

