#### Primary Outcome

The primary outcomes are the detection rate and PPV of DR and AMD screening.

Detection rate:

$$\frac{Number\;of\;people\;with\;the\;confirmatory\;diagnosis\;of\;AMD\;or\;DR}{Number\;of\;people\;who\;participate\;in\;screening}$$

PPV:

$$\frac{Number\;of\;cases\;the\;confirmatory\;diagnosis\;of\;AMD\;or\;DR}{Number\;of\;screened\;positive\;cases}$$

Detection rate is defined as the proportion of screened participants who receive a confirmatory diagnosis of DR or AMD among all participants who undergo screening. PPV is defined as the proportion of participants with a confirmatory diagnosis among those who test positive in the screening.

The intention-to-screen population will include all randomized participants, who will be analyzed according to their assigned group regardless of adherence to the screening or referral process. Missing outcome data, particularly those resulting from incomplete referral follow-up, will be addressed under the intention-to-screen principle and reflected in the detection rate. Specifically, participants who test positive but are not referred for confirmatory diagnosis will remain included in the denominator when calculating detection rates, although they will not contribute to the numerator. The per-protocol population will include participants who complete the screening and adhere to the predefined study procedures. Participants with incomplete referral follow-up who test positive but do not comply with referral for confirmatory diagnosis will be excluded from both the numerator and denominator when calculating the PPV.

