### Limitations

Although this study is designed as a low-risk pragmatic clinical trial, several limitations should be acknowledged. First, while detection rate and PPV provide meaningful indicators of real-world screening effectiveness and downstream care engagement, they do not capture all dimensions of screening accuracy or long-term patient benefit. Important outcomes such as false-negative rates, disease progression, visual outcomes, and treatment-related outcomes are not designated as central end points in this protocol. These outcomes represent important areas for future investigation beyond the scope of the current pragmatic trial. Nonetheless, these will be estimated using the simulation models. Second, follow-up data may be incomplete for participants who seek subsequent ophthalmologic care outside the NTUH health care system, Fu Jen Catholic University Hospital, and Min-Sheng General Hospital. In such cases, confirmatory diagnostic results and downstream clinical outcomes may not be fully captured, potentially limiting the completeness of outcome assessment. This issue will be evaluated in the subgroup analyses. Third, the AI-assisted screening tools evaluated in this study are designed to detect specific retinal conditions only, including the DR and AMD. Other ocular diseases or retinal pathologies are not within the diagnostic scope of these tools and therefore may not be identified through the AI screening process while they may be identified by physicians. These will be evaluated in the post hoc analyses. Fourth, suboptimal image quality and inherent limitations in AI-based interpretation may result in false-positive or false-negative screening results, which could lead to unnecessary referrals or missed cases. To reduce this risk, image quality will be monitored at the time of acquisition, with repeat imaging performed when necessary, and cases with uncertain findings will still be referred for ophthalmologic evaluation. The impact will be evaluated in the subgroup or post hoc analyses. Fifth, real-world health care system constraints may influence the effectiveness of the screening-to-referral pathway. Limited ophthalmology workforce capacity and outpatient clinic availability may affect referral completion and time to confirmatory diagnosis, particularly in high-volume clinical settings. These constraints reflect routine clinical practice and may impact the generalizability of study findings to health care systems with different resource availability. Finally, it is important to emphasize that the AI-assisted screening tools are intended to support, rather than replace, clinical judgment. Treating physicians and ophthalmologists retain full responsibility for diagnostic confirmation and treatment decisions. Medical personnel involved in the study will receive training on appropriate interpretation and use of AI-assisted outputs to ensure safe and effective integration into clinical care.

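### The per-protocol set used for PPV requires successful AI interpretation, which has no counterpart in the control arm, and it conflicts with the PPV rule and PPV status given elsewhere

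*Protocol article*

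**What the plan says.** **Status of PPV.** The Primary Outcome section states: "The primary outcomes are the detection rate and PPV of DR and AMD screening". The abstract also lists PPV among the primary outcomes. The Statistical Analysis section treats the detection rates as the primary estimates and says of the per-protocol set: "This population will be used to assess secondary outcome estimates, namely the PPVs". The Secondary Outcomes section names only cost-effectiveness.

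**Population for PPV.** Three descriptions are given.

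- Statistical Analysis, on the per-protocol set: only those "who adhered to the predefined study procedures, namely successful AI interpretation and, for those with positive test results, successful referral", with the further rule "Participants with any missing data during the process will be excluded from the per-protocol analysis".
- Statistical Analysis, later, on missing outcomes: "For PPV analyses, participants with missing confirmatory diagnosis will be excluded from both the numerator and denominator". No AI condition appears.
- Primary Outcome: a general per-protocol definition (screening completed, procedures followed). For PPV, it removes screen-positives who do not comply with referral. Again there is no AI condition.

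**AI in the control arm.** The Figure 4 text states: "In the control arm, images are not analyzed by AI". The AI Platform Functionality section likewise has the dispatcher hold back images from AI according to assigned arm.

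**Unreadable and uncertain images.** The subgroup list in Statistical Analysis foresees images for which AI still gives no report after repeat testing, without giving a rate. The Limitations section adds that "cases with uncertain findings will still be referred for ophthalmologic evaluation".

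**The concern.** Successful AI interpretation is known only after randomisation, and only in one arm. If it decides who enters the PPV analysis, the AI arm loses its hardest images while the control arm keeps equally hard ones. A PPV difference could then appear although both arms read images equally well. This matters because the outcome section names PPV as primary and the plan tests it between arms.

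The text also leaves open which PPV set will be used and whether PPV can support a primary claim. The planned image-quality subgroup does not settle this: it is defined by AI failing to report, so it too has no counterpart among controls, and it is exploratory. The regression models that adjust for image quality are labelled post hoc.

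**Working it through.** **1. The plan's own figures.** The protocol gives sample sizes for detection rate only. Unpooled two-proportion formula, two-sided alpha 0.05, power 90%, divided by 0.70 for referral:

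- DR, 10% v 15%: 915 / 0.70 = 1307.1 per group; stated 1306.
- AMD, 5% v 10%: 578 / 0.70 = 825.7 per group; stated 825.

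These reproduce to within about 1 per group and do not depend on the present point. No sample size or power is given for PPV.

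**2. Which exclusions act in which arm.**

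| Condition | AI arm | Control arm |
|---|---|---|
| Successful AI interpretation | can be met or failed | undefined |
| Successful referral if positive | applies | applies |
| No missing data | applies | applies |
| Confirmatory diagnosis present | applies | applies |

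Only the first row is unequal.

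**3. What the unequal row could do.** Both arms are given identical true accuracy, so any PPV difference is an artefact.

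Inputs:

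- Sensitivity 92.2% and specificity 89.5% for DR, from the section on performance of the tools.
- Prevalence 10% among readable images: an assumption, borrowed from the DR figure in Sample Size Estimation.
- Unreadable share u, proportion of unreadable images referred r, and proportion of them diseased d: not in the protocol, so varied.
- Referral completion is taken as equal in all cells, so it cancels.

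AI arm, unreadable images excluded:

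PPV = 0.10×0.922 / (0.10×0.922 + 0.90×0.105) = 0.0922 / 0.1867 = 49.4%.

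Control arm, unreadable images kept:

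PPV = [(1-u)×0.0922 + u·d·r] / [(1-u)×0.1867 + u·r].

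Example with u = 5%, r = 1, d = 10%: (0.08759 + 0.00500) / (0.17737 + 0.05000) = 0.09259 / 0.22737 = 40.7%. The artefact is 49.4 - 40.7 = +8.7 points.

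Results at u = 5%:

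| Unreadable images referred | Diseased among them | Control PPV | AI minus control |
|---|---|---|---|
| all | 10% | 40.7% | +8.7 |
| all | 20% | 42.9% | +6.5 |
| half | 10% | 44.5% | +4.9 |
| half | 20% | 45.8% | +3.6 |
| none called positive | 10% | 49.4% | 0 |
| all | 60% | 51.7% | -2.3 |

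The half-referred, 20% row is (0.08759 + 0.00500) / (0.17737 + 0.02500) = 0.09259 / 0.20237 = 45.8%.

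Over u from 2% to 15%, with all referred, the artefact runs from +3.9 to +19.1 points at 10% diseased, and from -1.0 to -5.2 at 60% diseased. The sign changes where PPV among unreadable images equals that among readable ones, here 49.4%.

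**4. After the change.** With one rule in both arms, the same strata enter both PPVs and this artefact is zero by construction.

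**The case against.** The strongest reply is that the protocol already holds an arm-neutral PPV rule, in Primary Outcome and again in the missing-data text, and that the general per-protocol definition makes an empty control arm a strained reading. That stands, and it is why this is partly a conflict between passages. It does not remove the problem, because the Statistical Analysis section attaches the AI condition to the very set in which PPV is to be assessed.

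A second reply is that poor images are retaken on site in both arms and that physicians may also flag them, so only residual failures count. This also stands; it makes u smaller, by an unknown amount.

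Three stronger readings are tempting, and the documents support none of them.

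- A reader might infer that the rule necessarily favours AI. That is the likelier direction, since uncertain cases are still referred, but the table shows zero and reversed results under inputs that the documents do not rule out.
- A reader might count two outcomes and two diseases as four tests and put the false-claim rate at 1 - 0.95^4 = 18.5%. That needs independent tests and a rule that any one success suffices. Detection rate and PPV share a numerator, participants may contribute to both diseases, and the protocol states no such success rule; one may sit in the SAP, which is not shown.
- A reader might want PPV replaced by unconfirmed referrals per randomised participant. That is a preference. It also leaves open how to count non-attenders, about 30% of positives under the protocol's 70% referral assumption.

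**Conclusion.** The defect is real as written. One condition for the PPV population exists in the AI arm only, depends on a post-randomisation event, and contradicts the PPV rule given twice elsewhere. PPV's status is also contradictory.

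The resulting bias is possible, and more likely toward AI than away from it, but neither size nor sign can be fixed from the protocol. At 5% unreadable images, the cases worked here with half to all referred and 10% to 20% diseased give about +4 to +9 points; other inputs give zero or about -2. These figures rest on the assumed 10% prevalence, the quoted DR accuracy applied to both arms, and equal referral completion.

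The detection-rate analysis keeps all randomised participants whether or not AI interpretation succeeds. It and its sample sizes are untouched.

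**What to change.** 1. In Statistical Analysis, delete successful AI interpretation from the population used for PPV. Apply the rule already in Primary Outcome and in the missing-data text to both arms: all screen-positive participants with a confirmatory diagnosis, by assigned arm. AI-arm participants whose images AI could not read stay in according to the physician's recorded screening decision.
2. If the set with successful AI interpretation is wanted, keep it at most as a labelled sensitivity analysis, and say that its restriction acts in one arm only.
3. State PPV's status once. Secondary agrees with Statistical Analysis; the abstract, Primary Outcome and Secondary Outcomes then need matching edits. Add that PPV conditions on post-randomisation events (screening positive and completing referral), so its between-arm difference is not a fully randomised comparison.

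The cost is wording, with no change to sample size or data collection. AI-arm PPV may look slightly less favourable, and PPV loses primary status. The edits are best made before the randomised phase starts.

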**Results:**

The study was funded in September 2024, began on October 2, 2025, and is expected to be completed in December 2027. After the pilot implementation phase without randomization, participants will be randomized 1:1 into two groups: (1) AI-assisted screening, and (2) usual physician-only screening. The primary outcomes will include the detection rates (defined as participants with confirmed DR or AMD among all screened participants) and the positive predictive values (defined as participants with confirmed DR or AMD among those who tested positive). Cost-effectiveness analyses will be performed using data derived from the trial results.

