### Randomization

Participants will be randomized at the individual level in a 1:1 ratio to either the AI-assisted screening group or the conventional physician-based screening group. Randomization is performed on a per-participant basis, and sample size estimation will be based on this process. DR and AMD are managed within a single unified cohort. DR and AMD can be diagnosed in the same patient, while DR and AMD are treated as separate disease-specific outcomes, and analyses will be conducted independently for each condition based on predefined eligibility criteria. Participants eligible for both conditions may contribute to both analyses.

In the conventional physician-based screening arm, fundus photographs will be interpreted by physicians without the use of any AI assistance. Physicians will review the images independently based on their clinical judgment. All physicians involved in image interpretation will receive standardized training in fundus photograph assessment prior to study initiation. In addition, a standardized reading guide will be provided to ensure consistency in image interpretation across the control group.

Randomization will be conducted using a computerized randomization module embedded within the rule engine of AIMIGS. After enrollment, each participant will be assigned a unique study ID, and allocation will be automatically generated by AIMIGS. Once the assignment is generated, the system automatically allocates each participant to the designated study arm and triggers the corresponding imaging procedures according to the predefined workflow.

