#### Secondary Outcomes

The secondary outcome is the cost-effectiveness of AI-assisted screening compared with conventional screening, assessed using the incremental cost-effectiveness ratio, under the societal perspective. Cost-effectiveness analyses will incorporate both the direct and indirect medical costs related to screening, diagnostic evaluation, and treatment.

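### PPV is a primary outcome in some sections and secondary in another, and at an unsplit .05 this moves the chance of a false-positive primary result within a disease from 5% to as much as 9.75%

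*Protocol article*

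**What the plan says.** Four places in the protocol article assign status to the outcomes.

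- **Abstract, Results:** "The primary outcomes will include the detection rates", and the same sentence adds the PPVs.
- **Primary Outcome:** "The primary outcomes are the detection rate and PPV of DR and AMD screening".
- **Secondary Outcomes:** "The secondary outcome is the cost-effectiveness of AI-assisted screening compared with conventional screening". PPV does not appear there.
- **Statistical Analysis:** participants with incomplete follow-through are still "included in the analysis of the primary outcome estimates, namely the detection rates". Of the per-protocol population it then says: "This population will be used to assess secondary outcome estimates, namely the PPVs".

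On testing, the Randomization section says of DR and AMD that "analyses will be conducted independently for each condition based on predefined eligibility criteria". Statistical Analysis compares the outcomes with two-sample proportion tests and sets one threshold: a two-sided P "value of <.05 will be considered statistically significant". Multiplicity is mentioned only for the exploratory subgroups, whose "results will be presented descriptively without adjustment for multiple comparisons". Sample Size Estimation sizes the detection comparison for each disease at two-tailed alpha .05 and 90% power. It gives no calculation for PPV.

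**The concern.** The statements about PPV cannot all be true. Under the abstract and the Primary Outcome section, each disease has two primary tests. Under Statistical Analysis it has one. Under Secondary Outcomes, PPV is not secondary either.

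The label matters because the two measures need not agree. A strategy that refers more people tends to raise detection and lower PPV; a more selective one does the reverse. With PPV primary and no statement of what counts as success, a trial that misses on detection but reaches P <.05 on PPV could be reported as positive on a primary outcome, and the text would support that report.

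PPV is also a weak candidate for that role. Its denominator is screen-positive participants, a group formed after randomisation and shaped by the intervention itself. Screen-positive participants without a confirmatory diagnosis are then dropped, about 30% of them under the protocol's own 70% referral assumption. The PPV comparison is therefore not between the groups as randomised. The intention-to-screen detection rate is.

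**Working it through.** **1. Was any adjustment built into the design?** The inputs from Sample Size Estimation are 10% versus 15% for DR, 5% versus 10% for AMD, alpha .05 two-tailed, power .90 and referral 70%. The unpooled two-proportion formula, with (1.960 + 1.282)² = 10.507, divided by 0.70 for referral, gives:

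- DR: 10.507 × (0.10×0.90 + 0.15×0.85) / 0.05² = 914.1; 914.1 / 0.70 = 1305.9 per group (stated 1306).
- AMD: 10.507 × (0.05×0.95 + 0.10×0.90) / 0.05² = 577.9; 577.9 / 0.70 = 825.6 per group (stated 825).

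Both figures reproduce with the full .05 for each detection test, so no alpha was set aside for a second primary test.

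**2. Chance of at least one false-positive primary result, all nulls true.** For k independent tests at .05 this is 1 − 0.95^k.

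| Reading | Primary tests | Chance |
|---|---|---|
| PPV secondary, one disease | 1 | 5% |
| PPV secondary, both diseases pooled | 2 | 1 − 0.95² = 9.75% |
| PPV primary, one disease | 2 | 1 − 0.95² = 9.75% |
| PPV primary, both diseases pooled | 4 | 1 − 0.95⁴ = 18.5% |

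For jointly normal two-sided statistics the independent case is the maximum. The tests will be correlated, since some participants count for both diseases and the two measures share confirmed cases. In simulation with an equal correlation of 0.5 (an assumption), four tests give 15.6% and two give 9.1%. These figures count errors in either direction. Counting only false results in favour of AI, at .025 per test, independence gives 1 − 0.975² = 4.9% and 1 − 0.975⁴ = 9.6%.

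**3. Can detection and PPV diverge?** At a given prevalence, PPV rises with sensitivity / (1 − specificity), so that ratio fixes the ordering of the arms.

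- AI arm, taking the reported software-alone DR accuracy of 92.2% and 89.5%: 0.922 / 0.105 = 8.78.
- Control arm: the protocol gives no reader accuracy. Assume sensitivity 92.2% × 10/15 = 61.5%, which mirrors the planned 10% to 15% detection ratio.
- The ratios are equal when 1 − specificity = 0.615 / 8.78 = 0.070, that is, at a control specificity of about 93.0%.

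At 10% prevalence the AI PPV is 0.0922 / (0.0922 + 0.0945) = 49%. For the control arm:

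| Assumed control specificity | Control PPV | AI PPV is |
|---|---|---|
| 90% | 0.0615 / (0.0615 + 0.090) = 41% | higher |
| about 93% | 49% | equal |
| 95% | 0.0615 / (0.0615 + 0.045) = 58% | lower |

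AI has the higher sensitivity in every row, so whether the two measures agree turns on a specificity that the documents do not give.

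**The case against.** The strongest reply is that the operative analysis text already points one way. The sample size rests on detection alone, the primary intention-to-screen analysis is tied to detection, and the missing-data paragraph again attaches the word primary to detection. On that reading PPV is secondary and each disease has one primary test at 5%. This has weight, and it supports the fix below. It does not remove the contradiction, because the section that formally defines the primary outcomes, and the abstract, say otherwise.

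A second reply is that multiplicity rules are commonly left to a statistical analysis plan, which is not shown. That is fair: the absence of a rule is not by itself the point. The point is what this document states, namely two incompatible labels for PPV alongside a flat .05.

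Three stronger readings are tempting, and the documents do not support them.

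- A reader might infer that any one claim carries an 18.5% risk of being false-positive. It carries 5%. The 18.5% is the chance of at least one error among four, and it requires pooling two diseases that the Randomization section treats as separate outcomes.
- A reader might infer that AI is likely to win on detection and lose on PPV. The worked range shows only that this can happen. The control reader is assumed, physicians rather than the software decide on referral in the AI arm, the example's implied detection rates before referral loss (9.2% versus 6.2%) are not the planned 15% versus 10%, and the protocol itself anticipates that both measures may improve.
- A reader might infer an intention to choose the headline after seeing the data. Nothing suggests that; the text merely fails to rule it out.

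Finally, the conditioning of PPV on a positive screen is a separate weakness. It bears on which outcome should be primary, not on the error rate.

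**Conclusion.** The concern holds as an explicit inconsistency with a bounded consequence. Depending on which section is followed, the chance of at least one false-positive primary result within a disease is 5% or up to 9.75%. Only if DR and AMD are combined into one trial-level claim do these become up to 9.75% and up to 18.5%. The upper figures assume all nulls true and independent two-sided tests, and correlation lowers them. Every individual test remains valid at 5%. That detection and PPV can disagree is established as a possibility; how likely it is depends on control-reader specificity, with the switch near 93% under the stated assumptions. The matter should be corrected before outcome data are compared between arms, because the label given to PPV can decide whether the trial is reported as a success.

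**What to change.** 1. State the intention-to-screen detection rate as the single primary outcome for each disease.
2. State PPV as a secondary outcome, tested at .05 only if detection is significant for that disease, and otherwise reported with its confidence interval and no claim. This holds the error rate for the two measures at 5% within each disease.
3. State that DR and AMD each support only their own disease-specific claim at .05. The chance of an error in at least one disease then remains up to 9.75%, which is acceptable if no pooled claim is made.
4. Align the abstract, Primary Outcome, Secondary Outcomes and Statistical Analysis sections accordingly.

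**Cost.** The change is one of wording and needs no extra participants. The 90% design power of each detection test is unchanged. What is lost is any stand-alone claim on PPV.

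**Alternatives cost more.** Splitting .05 equally over four primary tests would cut detection power at the stated sizes to about 77% in each disease (pooled-variance formula, 70% of the stated numbers); restoring 90% would take 1783 per group for DR and 1130 for AMD. A fixed DR-then-AMD sequence for one overall claim is best left out. If it is used, the protocol should say that power for AMD falls to about 0.90 × 0.90 = 81% if the two tests are independent.
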